## Abstract

Intra‐operative hypotension is common and associated with postoperative organ injury and mortality, particularly in older patients living with frailty. Continuous invasive arterial blood pressure monitoring provides real‐time measurements and may allow earlier detection and management of hypotension and improve outcomes. Contemporary UK data show that this intervention is rarely used in elderly patients living with frailty who are undergoing urgent hip fracture surgery. The CAREFUL Study (**C**ontinuous **AR**terial monitoring in **E**lderly and **F**rail patients for hip fract**U**re surgery to prevent **L**ow blood pressure) will synthesise evidence to determine the feasibility of a definitive randomised controlled trial evaluating continuous versus intermittent arterial blood pressure monitoring in this population. The study comprises three integrated workstreams: a systematic review and meta‐analysis to evaluate existing evidence on continuous arterial blood pressure monitoring and peri‐operative outcomes; mixed‐methods qualitative analysis to explore clinician attitudes, barriers and facilitators to implementation; a multi‐centre external feasibility randomised controlled trial with embedded qualitative research. The feasibility study will randomise 100 patients aged ≥ 65 years with a Clinical Frailty Scale score of ≥ 5 undergoing proximal femoral fracture surgery to either continuous invasive arterial blood pressure monitoring or non‐invasive 3‐ to 5‐minute cycle blood pressure monitoring. Data will include recruitment, retention and intervention compliance, exposure to intra‐operative hypotension, postoperative complications and quality of life. Findings will inform the design of a definitive effectiveness trial. Results will be shared through peer‐reviewed open‐access publications, stakeholder events and collaboration with professional bodies and patient partners to guide future peri‐operative care for older, frail surgical patients.

## Introduction

Intra‐operative hypotension occurs in up to two‐thirds of operations [1] and is associated with harm, particularly in high‐risk patient groups [2]. Large systematic reviews and meta‐analyses show that the severity of hypotension, both in terms of depth and duration, is linked to renal, cerebral and myocardial injury and mortality [2]. Patients at high risk of harm include those who are older (≥ 65 years) and living with frailty [3, 4]. This older and frail group represents one in four patients over 65 years presenting for surgery in the United Kingdom, rising to over 60% of those aged > 85 years [5], and will likely increase in number in the future [6, 7]. Notably, patients requiring surgery for proximal femoral fracture (PFF) are firmly in this demographic. Of over 70,000 patients with PFF having surgical treatment annually in England, Wales and Northern Ireland, 30‐day mortality is 6% and 1‐year mortality is up to 30% [8, 9].

In the United Kingdom, the minimum acceptable monitoring standard during anaesthesia includes intermittent non‐invasive blood pressure monitoring (typically every 3–5 minutes). National guidelines advise that additional invasive monitoring should be considered when there is cardiovascular comorbidity, frailty or the surgery is urgent [10]. However, recent data from the Royal College of Anaesthetists (RCoA) 7th National Audit Project (NAP7) on peri‐operative cardiac arrest highlights that this is not occurring in older frail patients, particularly those presenting for PFF surgery [5, 11, 12]. The report concluded that patient harm, including deaths, may have been prevented with increased rates of continuous invasive arterial blood pressure monitoring [5, 6, 12, 13, 14]. A key recommendation was that further research should evaluate if continuous blood pressure monitoring, as an intervention, is beneficial in this population [12].

Here, we aim to combine three complementary work streams to generate evidence, asking ‘*Does continuous arterial blood pressure monitoring during surgery benefit patients who are high risk, particularly those who are older and living with frailty?*. We will:Undertake a systematic review and meta‐analysis to examine the current evidence base regarding the impact of continuous blood pressure monitoring on intra‐operative hypotension and associated morbidity and mortality.Understand clinician attitudes towards continuous arterial monitoring in older frail patients presenting for trauma surgery through mixed‐methods qualitative research.Undertake a feasibility study with embedded qualitative research to assess whether a full‐scale definitive randomised controlled trial (RCT) of continuous invasive arterial blood pressure monitoring versus standard care is feasible in the older, frail patient population presenting for hip fracture surgery.

## Methods

### Work package 1: systematic review

The systematic review will ask: ‘*Does continuous arterial blood pressure monitoring prevent exposure to intra‐operative hypotension and reduce morbidity and mortality?*’ and has been prospectively registered with PROSPERO (CRD42025648753). The review will be reported to PRISMA (Preferred Reporting Items for Systematic reviews and Meta‐Analyses) standards [15].

We will search databases including MEDLINE, EMBASE, PubMed, ClinicalTrials.gov and the WHO International Clinical Trials Registry Platform for studies reported in English. Observational data and RCTs will be included. Studies will also be identified through reference and citation tracking of included articles. Study authors may be contacted to request further information. The following search terms will be used: [((intra‐arterial) OR (continuous blood pressure) OR (invasive blood pressure) OR (arterial cannulation) OR (clearsight) OR (nexfin) OR (continuous non‐invasive) OR (continuous non‐invasive) OR (CNAP)) AND ((intra‐operative hypotension) OR (intraoperative hypotension) OR (hypotension)) AND ((anesthesia) OR (anaesthesia) OR (surgery))].

The review will include RCTs and observational data, such as cohort studies, but will exclude case studies and case series. Participants will be adult patients (≥ 18 years) undergoing a surgical procedure under the care of an anaesthetist and receiving any form of general anaesthesia and/or neuraxial anaesthesia (spinal, epidural or combined spinal‐epidural). Studies will be excluded if they focus solely on children (≤ 17 years), anaesthesia or sedation which is not intended to enable surgery, patients who are already anaesthetised before transfer to the operating theatre complex, anaesthesia not administered by anaesthetists, sedation only and non‐human studies.

The intervention to be examined will be the use of continuous arterial blood pressure monitoring in adult patients undergoing surgery using either non‐invasive or invasive monitoring and will be compared to standard care, namely intra‐operative blood pressure monitoring with non‐invasive intermittent (typically 3‐ to 5‐minute cycles) oscillometric blood pressure monitoring. Outcomes will include exposure to intra‐operative hypotension (time weighted average of mean arterial blood pressure less than 65 mmHg); morbidity, including rates of acute kidney injury, myocardial injury and delirium; and mortality. The outcomes are detailed in Supporting Information 1.

The review will be managed using Covidence (Covidence systematic review software, Veritas Health Innovation, Melbourne, Australia. Available at www.covidence.org). Following de‐duplication, titles and abstracts, followed by remaining full‐text articles, will be screened against the inclusion criteria by two reviewers, with a third assessor to resolve disagreements. All efforts will be made to retrieve the full‐text articles of potentially eligible articles.

Data extraction will occur independently by two reviewers in duplicate. A PRISMA flow diagram will illustrate the process.

Key study, participant and quality measures will be presented. Data from RCTs will be pooled in a random‐effects meta‐analysis, provided there are sufficient RCTs. Data for each measure will be presented as pooled odds ratios, mean differences or standardised mean differences, along with the associated 95% confidence intervals. A narrative synthesis of study results will be performed if substantial clinical or methodological heterogeneity is observed. A meta‐analysis may not be performed if substantial clinical or methodological heterogeneity is observed. All studies included in the analysis will be reviewed according to the Cochrane risk‐of‐bias tool 2 for randomised trials [16].

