### Progression criteria

The feasibility study is not powered to detect any difference in clinical or patient‐focused endpoints. Therefore, progression criteria will centre on the deliverability of a definitive trial through evidence obtained in all three work packages. Progression criteria include:Work package 1: The systematic review supports that there is a lack of evidence in this area.Work package 2: Survey and qualitative interviews do not raise significant concerns about acceptability of the intervention to patients and carers, and clinical equipoise or barriers to large‐scale intervention implementation.Work package 3: We will use a red‐amber‐green rating system to classify key elements of feasibility (see Table 1). These will be:○
Site setup: Four sites setup and recruiting patients○
Recruitment: An average of two participants per site recruited per month, ensuring planned recruitment within 15 months.○
Data collection: We anticipate a complete capture of patient‐reported outcome measures (EQ‐5D) at 120 days from 70% or more patients or their proxy.○
Intervention compliance: High rates of intervention compliance and delivery (> 80%).
If all scores are green, this will support progression towards a full trial. Amber scores will indicate that some modifications may be required for a full trial. Any red score will signal concern over feasibility. If none of the scores are green, combined learning from the nested qualitative study and work packages 1 and 2 may indicate how to overcome aspects of feasibility, which may provide reassurance for progression.

**Table 1 anr370059-tbl-0001:** Indicative progression criteria for feasibility. These criteria will be considered alongside findings from the systematic review and the mixed‐methods study to inform progression to a definitive randomised controlled trial.

Domain	Target at end of trial	Green	Amber	Red
Site setup	Four sites setup and recruiting first participant	100% (4 sites)	50–99% (2–3 sites)	< 50% (1 site)
Participant recruitment	Average of 2 participants recruited per site per month	100% (2 per month)	50–99% (1.0–1.9 per month)	< 50% (< 1 per month)
Outcome follow‐up data	Collect ≥ 70% of participant‐reported outcome data at 120 days	≥ 70% (≥ 70 patients)	50–69% (50–69 patients)	< 50% (< 50 patients)
Intervention compliance	≥ 80% of participants receive allocated treatment	≥ 80% (≥ 80 patients)	50–79% (50–79 patients)	< 50% (< 50 patients)

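### The review's search string makes a hypotension term compulsory, so eligible studies reporting only morbidity or mortality can be missed, which leans towards the progression criterion of little evidence

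*Protocol article*

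**What the plan says.** All of the following is in the Protocol article.

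- **Question** (Work package 1: systematic review). The review asks whether continuous monitoring will "prevent exposure to intra‐operative hypotension and reduce morbidity and mortality".
- **Outcomes** (same section). Besides exposure to hypotension, they include "morbidity, including rates of acute kidney injury, myocardial injury and delirium; and mortality". Details are left to Supporting Information 1.
- **Search** (same section). The string is introduced by "The following search terms will be used" and printed in full. It has three blocks: monitoring terms, then "AND ((intra‐operative hypotension) OR (intraoperative hypotension) OR (hypotension)) AND", then anaesthesia or surgery terms. The join between the last two blocks reads "hypotension)) AND ((anesthesia) OR (anaesthesia) OR (surgery".
- **Supplementary route** (same section). "Studies will also be identified through reference and citation tracking of included articles". Study authors may also be contacted.
- **Use of the result** (Progression criteria). The criterion for this work package reads "The systematic review supports that there is a lack of evidence in this area".

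**The concern.** The question and the outcome list treat clinical harm as an outcome in its own right. The search admits a record only if it mentions one particular outcome, hypotension. A trial or cohort study that compares monitoring methods and reports deaths, delirium or organ injury would be eligible on the stated criteria, yet it fails the string unless hypotension is also mentioned.

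Two things are at stake. First, if the review finds few data on morbidity and mortality, a reader could not tell whether that reflects the literature or the search. Second, the review feeds a decision in which finding little counts towards going ahead, so any error of this kind leans one way.

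**Working it through.** No sample size, error rate or event count is involved, and the plan gives no figure to reproduce. The check is one of logic.

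**1. Structure of the string.** Let M be the monitoring block (nine printed terms, one of them repeated), H the hypotension block and S the anaesthesia or surgery block. A record is retrieved if M AND H AND S.

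**2. Reduction of H.** H has three terms joined by OR: hypotension alone, and hypotension preceded by each of two spellings of intra-operative. The two longer terms are special cases of the single word, so H reduces to *hypotension*. No clinical outcome can stand in for it.

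**3. Question against search.**

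| Outcome in the review | Can a record reporting only this outcome satisfy H? |
|---|---|
| Exposure to hypotension | Yes |
| Acute kidney injury | Only if hypotension is also mentioned |
| Myocardial injury | Only if hypotension is also mentioned |
| Delirium | Only if hypotension is also mentioned |
| Mortality | Only if hypotension is also mentioned |

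**4. Test of the rule.** The string was applied to four invented records. Each satisfies M and S.

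| Invented record | As printed | H widened by OR to the clinical outcomes | H dropped |
|---|---|---|---|
| Invasive pressure, surgery; hypotension and kidney injury | retrieved | retrieved | retrieved |
| Invasive pressure, surgery; kidney injury and mortality | not retrieved | retrieved | retrieved |
| Continuous non-invasive pressure, anaesthesia; delirium | not retrieved | retrieved | retrieved |
| Arterial cannulation, anaesthesia; myocardial injury | not retrieved | retrieved | retrieved |
| Total | 1 of 4 | 4 of 4 | 4 of 4 |

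The records were made up to exercise the rule. The totals show how the string behaves and say nothing about the share of real studies lost.

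**5. Direction.** For losses due to this block, studies found = eligible − lost + recovered by tracking, with lost ≥ 0 and recovered ≤ lost. So studies found ≤ eligible: the block can remove evidence but cannot add any. Tracking starts from articles already included, most of which will have come through the same filter, so full recovery cannot be assumed.

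**The case against.** **The narrower aim.** The Introduction describes the review as concerning hypotension and the harm associated with it, and the article's rationale runs from monitoring through less hypotension to less organ injury. On that reading, requiring the intermediate concept is a defensible way to keep the search precise. This explains the string but does not settle the matter: the formal question and the outcome list carry no such restriction.

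**Most relevant studies may mention hypotension.** A study with kidney injury or death as its main outcome is still retrieved if the word appears once in the searched fields, and the article does not say which fields those are. This stands. A reader might infer that morbidity and mortality studies *are* missed as a class; the document supports only that some *can* be.

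**The link to progression is loose.** The criterion has no threshold, it is one of several considered across three work packages, and the Discussion places the gap in older, frail patients needing urgent surgery, whereas the review covers adults having any surgery under general or neuraxial anaesthesia. A lost study of elective surgery might not change the judgement. This stands as a limit on consequence but does not change the direction of the error.

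**Other inferences to avoid.** Counting how many outcomes lack a search term does not measure the loss: a search with no outcome block at all would name none of them and would be wider. The repeated term for continuous non-invasive monitoring may be a typographical effect; a duplicate joined by OR removes no record.

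**Conclusion.** The mismatch between the review's question and its search is real and stands in the printed text. It does not come from condensing a longer protocol, because the string is given in full as the one to be used. Followed as written, the database search can lose eligible studies of morbidity or mortality, and any loss moves the review towards the finding that favours progression.

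The size is unknown. It could be close to nil if all fields are searched or nearly every relevant study mentions hypotension, and larger if only titles and abstracts are searched. A reader might infer that the criterion will be met because of the search; the document does not show that any lost study would reverse it.

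The conclusion assumes that the string is run as printed and that Supporting Information 1, which is not shown, does not confine the clinical outcomes to studies that also report hypotension. The point concerns the review and its use in the progression decision; it leaves the design and analysis of the randomised feasibility trial untouched.

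**What to change.** Keep the three-block structure and widen the second block with OR to the review's own named outcomes: acute kidney injury, myocardial injury, delirium and mortality, alongside hypotension. State the fields searched in each source. If the search has already been run, rerun the widened string, screen only the added records, and record the change as a PROSPERO amendment.

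The cost is more titles and abstracts for the existing two reviewers, with lower precision; the document gives no basis for estimating how many. Dropping the block outright would also cure the mismatch, but broad monitoring terms such as *intra-arterial* would then admit records that have nothing to do with blood pressure monitoring, so widening to the named outcomes is the better trade.

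If the narrower scope in the Introduction is what was meant, the alternative is to restrict the question and outcomes to match, and to read the progression criterion as covering that scope only. That needs no extra screening, but the review could then not support a statement about morbidity and mortality evidence in general.

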### Work package 2: mixed‐methods qualitative study

An online survey to determine current practices and attitudes of practicing anaesthetists towards continuous blood pressure monitoring in this patient group, with qualitative interviews.

We will aim to explore:respondent's experience in anaesthesia;experience of managing older frail patients;individual thresholds for arterial monitoring;perceived benefits, risks and harms of arterial monitoring;views on key outcome measures for a definitive study;equipoise and willingness to participate in a RCT.

We aim to survey anaesthetists of all grades (consultants, doctors in training and non‐consultant grades) who are currently practicing in the United Kingdom. National distribution networks (resident doctor networks, RCoA and the Association of Anaesthetists) will be utilised to ensure a large, representative sample of active anaesthetists based on previous experience.

Three focus groups (comprising 3–7 participants per group, approximately 15 participants in total) will be conducted. Key stakeholders (anaesthetists, orthopaedic surgeons, orthogeriatric physicians, operating department practitioners, representatives of the RCoA and Centre for Peri‐operative Care) will discuss clinical decision‐making regarding intra‐operative blood pressure monitoring and ascertain facilitators and barriers to running a full‐scale trial and the potential of changing practice.

The focus groups will explore the capacity and willingness to participate in a trial in the context of other ongoing trials in anaesthesia and the scope of inclusion criteria. We are interested in the potential reasons that prevent the wide‐scale implementation of continuous monitoring before and after trial evidence is available, as well as implementation issues. We will ascertain professional stakeholder views on aspects of trial design, including eligibility criteria and outcome measures.

### Work package 3: feasibility study

A feasibility study consisting of an external, multi‐centre, two‐arm, parallel‐group, assessor‐blinded randomised pilot trial with a nested qualitative study will be undertaken to determine the:feasibility of patient recruitment, intervention delivery, crossover rate, retention rates and completion of data collection;acceptability of the intervention to patients and carers;optimum primary outcome measure;feasibility of collecting health economic measures to inform the cost‐effectiveness evaluation in the main trial;feasibility of blinding outcome assessors to trial allocation.

### Setting

The study will be set in up to four National Health Service (NHS) hospitals in the UK providing anaesthesia and surgery for proximal femoral fracture.

### Inclusion criteria

Patients who meet all the following criteria will be considered eligible for the study:≥ 65 years old;clinically frail – assessed as a Clinical Frailty Scale (CFS) Score of ≥ 5 [3];primary hip (proximal femoral) fracture.

### Exclusion criteria

Patients who meet any of the following criteria will not be considered eligible for the study:planned continuous arterial blood pressure monitoring or use of non‐invasive blood pressure monitoring at a high frequency (1‐minute cycles) throughout the case;declining consent.

### Intervention and comparator

Following the randomisation procedure below, participants will be allocated to either:

*(A) Continuous invasive arterial blood pressure monitoring*
Up to three attempts to establish continuous invasive arterial blood pressure monitoring using local anaesthesia before general, neuraxial or regional anaesthesia.Continuous arterial blood pressure monitoring will be maintained until the patient reaches the recovery room, where it may be discontinued or continued at the discretion of the clinical team.

Or

*(B) Standard care*
Three‐ to five‐minute cycles of non‐invasive blood pressure monitoring.

### Timeline and outcomes

The main outcome is to assess feasibility. All data fields to be collected are described in Supporting Information 2 and the key study timepoints are shown in Fig. 1. Given the emergency setting of the study, eligibility, consent and randomisation may all occur on the day of surgery (day 0). A structured medical history will be recorded at the point of consent, and patient‐ or carer‐reported outcome measures (EQ‐5D) will be collected from pre‐fracture status. Delirium screening using the 4AT tool will occur before surgery and on day 3 (±1). Intra‐operative management and blood pressure will be recorded along with intervention compliance on the day of surgery. At 120 days, we will record mortality, the occurrence of major complications, days alive and at home in the original place of residence and patient‐ or carer‐reported outcomes (EQ‐5D).

